The primary objective of the trial is to determine whether the integrated ID/SUD care team intervention (SIRI team) will be associated with lower mortality and fewer hospital readmissions compared to TAU. The primary hypothesis is that the proportion of participants alive with no hospital readmissions will be higher in the SIRI team intervention group vs. TAU group at 4 months post-randomization. Secondary objectives are to examine differences between the two study groups in important milestones that may contribute to post-discharge recovery, harm reduction, and sustained health: proportion of participants alive with no hospital readmissions at all time points (4, 8, and 12 months post-randomization) to ascertain whether differences maintain during follow-up, completion of antibiotic course, initiation of treatment of SUD by hospital discharge, receipt of outpatient care post-discharge, retention in or completion of outpatient care, and change in substance use severity and frequency. Because the primary outcome is broadly defined as no hospital readmission and being alive (compared to any hospital readmission or all-cause mortality), we will examine more detailed sources of differences between the two groups as secondary outcomes: all-cause mortality, drug use-related mortality (infections or overdose), recurrent SIRI, and hospital readmission and emergency department visit number, type, and length. Additionally, the study’s economic evaluation will estimate the cost required to implement and sustain the SIRI team intervention and determine the relative value of the intervention from the healthcare sector and societal perspectives. The study’s simulation modeling will use healthcare utilization and health outcome data to estimate the long-term clinical- and cost-effectiveness of the intervention at a population-level. The objective of the implementation evaluation component is to understand preliminary determinants and strategies that lead to successful reach, adoption, implementation, and sustainability of the SIRI team intervention.

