Non-fatal overdose	Combination of medical record abstraction and self-report	4, 8, and 12 months
Mortality All cause •All cause •Substance use-related (SIRI, overdose)	Combination of medical record abstraction and other sources (e.g., coroner’s report)	Continuous
Substance use severity and frequency	Drug Abuse Screening Test, Alcohol Use Disorders Identification Test, and Addiction Severity Index	4, 8, and 12 months
Initiation of SUD treatment before hospital discharge •MOUD •MAUD	Medical record abstraction	n/a
Initiation of ID treatments before hospital discharge • ART/PrEP • HCV DAAs • Immunizations	Medical record abstraction	n/a
Receipt of post-discharge SUD treatments •MOUD •MAUD •Intensive outpatient •Mutual support •Residential treatment	Combination of medical record abstraction, self-report, and urine test for methadone and buprenorphine	4, 8, and 12 months
Receipt of post-discharge infectious disease treatments	Combination of medical record abstraction and self-report	4, 8, and 12 months
Service utilization measures •Length of stay •Patient directed discharge •Readmissions (count and binary) •ED visits (count and binary)	Combination of medical record abstraction and self-report	4, 8, and 12 months

ED, emergency department; HCV DAAs, hepatitis C virus direct acting antivirals; HIV, human immunodeficiency virus; MAUD, medication for alcohol use disorder; MOUD, medication for opioid use disorder; PrEP, HIV pre-exposure prophylaxis; SIRI, severe injection-related infection; SUD, substance use disorder

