For the primary outcome, data lost to missed visits will be supplemented via external records. Confirmation of death from any cause or of participant hospital readmission from the EHR abstraction will be considered a failure. If a participant is lost to follow-up and no records (EHR, medical examiner, emergency contacts’ report) are found to show death or readmission for the duration of the study, the outcome will be considered a success. Missing data is only anticipated for 1) participants who withdraw from the study up to and including study day 122 and who have not signed the consent addendum expressly permitting abstraction to continue, or 2) participants who withdraw from the study at any time during the follow-up period AND who have not signed the consent addendum AND EHR abstraction has not been performed up to and including study day 122 prior to the participant’s withdrawal. At baseline, participants will sign releases for all local health systems that they typically visit. These records will be supplemented by a query of EHR integration services, such as CareEverywhere in Epic Systems. For participants who miss their 4 month visit but attend the 8 or 12 month visit, they will be asked about readmissions dating back to the time of randomization.

A secondary analysis of the hospital readmissions across all time points will be conducted. For this analysis, a Generalized Estimating Equations (GEE) model will be employed with a binomial distribution and logit link as implemented in SAS for the secondary outcomes of proportion of participants alive with no hospital readmissions utilizing all time points. A GEE model is used to control for correlation associated with repeated measures within an individual since the analysis will be a longitudinal one at 4-, 8-, and 12-months. The model will include fixed effects for treatment group, time, the treatment-by-time interaction, site, type of primary drug use (opioid versus non-opioid), and admission to ICU as part of the index hospitalization (ICU versus non-ICU)). The secondary outcome hypotheses are that the proportion of participants alive with no hospital readmissions will be higher in the SIRI Team intervention group vs. TAU group at eight months (and, separately, at twelve months) post-randomization). These two hypotheses will be evaluated each using a two-sided test with an a priori alpha (i.e., type I error) of 0.05.

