Additional secondary analyses will utilize the methods for the primary analysis if they are a single dichotomous outcome. If they include repeated measures, they will follow the analysis strategy of the above secondary outcome description.

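### The rule for repeated secondary outcomes carries a binomial-logit GEE, with no baseline score, over to visit counts and severity scores that it does not suit

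*Protocol article*

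**What the plan says.** In the protocol article, Analyses of primary and secondary outcomes, the closing paragraph has two branches.

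- Single outcomes: "Additional secondary analyses will utilize the methods for the primary analysis if they are a single dichotomous outcome".
- Repeated outcomes: "If they include repeated measures, they will follow the analysis strategy of the above secondary outcome description". This branch carries no condition on the type of outcome.

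The description referred to is the longitudinal analysis of being alive without readmission: "a Generalized Estimating Equations (GEE) model will be employed with a binomial distribution and logit link". Its covariates are listed: "The model will include fixed effects for treatment group, time, the treatment-by-time interaction, site, type of primary drug use", followed by ICU admission. The time points are 4, 8 and 12 months; baseline is not among them.

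Table 2 (Outcomes) gives the following the time points 4, 8 and 12 months:

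- Substance use severity and frequency, measured by "Drug Abuse Screening Test, Alcohol Use Disorders Identification Test, and Addiction Severity Index".
- Service utilization, whose readmission entry begins "Readmissions (count and binary". Emergency department visits are labelled the same way, and length of stay is in the same row.

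Study design and objectives states one aim as "change in substance use severity and frequency". Measures and timing of follow-up assessments, with Table 1, has the DAST-10, AUDIT and ASI recorded at baseline as well as at every follow-up visit.

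**The concern.** A binomial model with a logit link describes a mean between 0 and 1. A number of readmissions, a number of emergency visits and a questionnaire score are not of that form. Anyone applying the rule as written must either cut these outcomes to yes/no, and lose information, or depart from the published plan and choose a model later.

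The covariate list raises a second issue. An outcome described as change is to be analysed with neither its starting value as a covariate nor baseline as a response time, although that value is on file for each participant.

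These outcomes are there to explain the primary result: the article says the broad composite will be broken down into more detailed sources of difference. Weak or improvised analyses of them would make the primary result harder to interpret.

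**Working it through.** **1. The plan's own figure.** The only power figures (Table 3) concern the binary primary outcome. Assuming 240 per arm (the article states two parallel arms but no ratio) and two-sided alpha 0.05, take the row 0.450 versus 0.578:

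- Pooled proportion 0.514; null SE = √(2 × 0.514 × 0.486 / 240) = 0.0456.
- Alternative SE = √((0.45 × 0.55 + 0.578 × 0.422) / 240) = 0.0452.
- Power = Φ((0.128 − 1.96 × 0.0456) / 0.0452) = Φ(0.85) = 0.80.

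All eight rows give 0.798 to 0.803, so Table 3 reproduces. It says nothing about counts or scores, and nothing below changes it.

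**2. Matching Table 2 to the rule.**

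| Outcome at 4, 8, 12 months | Type | Suits a binomial-logit GEE? |
|---|---|---|
| Readmission, ED visit (binary version) | yes/no | Yes |
| Readmission, ED visit (count version) | count | Not without dichotomising |
| DAST, AUDIT, ASI | score | Not without dichotomising |
| Length of stay | duration | No, if meant as repeated; if it is the index stay alone, neither branch covers it |

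Two other models in the article do not fill the gap. The Poisson model is an optional risk-ratio estimate for the binary primary outcome, and the GLMM belongs to the economic evaluation.

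**3. What the literal model does.** A binomial-logit GEE was fitted to simulated data for 480 participants at three visits (in Python, not SAS, so this shows the principle only).

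- 0–10 scores: no convergence and no estimates.
- Counts with control mean 0.6 and true rate ratio 0.7: it converged, because the mean lay below 1. The treatment coefficient was −0.663, and exp(−0.663) = 0.52. The fitted means at the first visit were 0.609 and 0.445, a ratio of 0.73. The coefficient is therefore a difference in logits of mean counts, not a log rate ratio.

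**4. Cost of cutting a count to any/none.** All inputs are assumed: rate ratio 0.7, 240 per arm, one period, gamma-distributed heterogeneity between participants with shape k, 400 simulated trials per row (Monte Carlo SE at most √(0.25/400) = 0.025). The count model is log-link Poisson with robust standard errors.

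| Control mean | k | Power, count model | Power, any/none |
|---|---|---|---|
| 0.5 | 0.5 | 0.46 | 0.31 |
| 0.5 | 1 | 0.54 | 0.45 |
| 1 | 0.5 | 0.59 | 0.34 |
| 1 | 1 | 0.74 | 0.48 |
| 2 | 0.5 | 0.68 | 0.32 |
| 2 | 1 | 0.88 | 0.43 |

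**5. Cost of leaving out the baseline score.** With baseline to follow-up correlation r (assumed), baseline as a covariate multiplies the residual variance by 1 − r². A plain change score multiplies it by 2(1 − r). The difference detectable with 80% power at one time point, with all 480 analysed, is (1.960 + 0.842) × √(4/480) = 0.256 SD unadjusted, and 0.256 × √(1 − r²) adjusted.

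| r | 1 − r² | 2(1 − r) | Detectable difference, adjusted (SD) |
|---|---|---|---|
| 0.3 | 0.91 | 1.40 | 0.244 |
| 0.5 | 0.75 | 1.00 | 0.221 |
| 0.7 | 0.51 | 0.60 | 0.183 |

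The covariate form is never worse than no adjustment. A plain change score is worse than no adjustment when r is below 0.5.

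**The case against.** The best defence is that the sentence carries over a strategy, not a distribution. The article says it chose GEE to handle correlation within a person, and it specifies the binomial form when describing one binary outcome. On that reading a count or score would use a GEE with its own distribution and link. Alternatively, the second branch may be meant only for repeated dichotomous outcomes, as the counterpart of the first. The article also condenses a fuller protocol, and an analysis plan may exist; neither is shown.

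Part of this stands. The looser reading is possible, and a fuller document may already name suitable models. But the article states neither limit, and its second branch covers repeated outcomes of any kind. This is an assigned model, not silence. Even on the loose reading the carried-over covariate list has no baseline score.

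A reader might infer more than the documents support:

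- **That the model cannot be fitted to any of these outcomes.** The binary versions fit the rule, and a low-mean count may return estimates, as step 3 shows.
- **That the article wrongly omits a time-at-risk offset for counts.** It names no count model, so it neither adopts nor rejects one. The choice is also debatable: the article says the intervention's antibiotic options may shorten hospital stay, so treatment could change such an offset.
- **That weighting or imputation is missing for these outcomes.** That is detail an article commonly leaves to the analysis plan, and utilization comes partly from record abstraction rather than visits alone.
- **That the mortality analysis is at fault.** Nothing in the article shows this.

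**Conclusion.** The point holds as a badly fixed rule for non-binary repeated secondary outcomes: the readmission and emergency-visit counts, the DAST, AUDIT and ASI scores, and length of stay if it is meant as repeated. For these the stated model is unsuitable unless they are dichotomised, and the scores are analysed for change without their baseline values.

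The consequence is lost information and precision. Randomisation keeps the comparison of arms unbiased without baseline adjustment, so it would be wrong to read this as a bias finding. The primary outcome, Table 3 and N = 480 do not change.

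The size rests on assumed inputs, since the documents give no correlations or event rates. Baseline adjustment gives a residual variance factor of 0.91 to 0.51 for r of 0.3 to 0.7, so the gain may be as small as 9%. In the count scenarios power is 0.46 to 0.88 with a count model, against 0.31 to 0.48 after cutting to any/none.

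**What to change.** Replace the repeated-measures sentence with a rule by outcome type:

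- **Repeated binary outcomes:** keep the binomial-logit GEE as described.
- **Readmission and emergency-visit counts:** a log-link count model, either negative binomial or Poisson GEE with robust standard errors.
- **DAST, AUDIT and ASI scores:** a linear repeated-measures model with the baseline score as a covariate, alongside the terms already listed.
- **Length of stay:** say whether it is the index stay or a repeated measure, and name a skew-appropriate model.

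If the full protocol or analysis plan already does this, align the article's sentence with it. The cost is a short change of wording and standard procedures; no new data are needed. It should be settled before outcome data by arm are seen, so that the models are not chosen after the fact.

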#### Implementation evaluation analyses

With participants’ consent, all interviews will be audio-recorded and transcribed verbatim for thematic analysis. The audio recordings will then be sent to a transcription company for transcription for data analysis purposes. Transcript data will be analyzed using an iterative, inductive approach drawing on primarily content analysis. One member of the research team will read a subsample of interviews and will develop a provisional coding scheme to identify what the participants perceived to be concerns or facilitators related to their participation, at the participant-level or the key informant-level. A second research team member will review a different subsample to validate the adequacy of the provisional coding scheme as well as identify any additional codes that may be appropriate. Categories will be reviewed and any determined to be conceptually overlapping will be collapsed. Subsequently, using a finalized coding scheme, all interviews will be independently coded by two research team members. Kappa will be calculated to measure inter-rater agreement on the coding of the interview transcripts. Text relevant to code will be excerpted for analysis and interpretation by the research team and described according to the PRISM domains and constructs. We will use a software program for qualitative analysis of textual data (e.g., NVivo).

#### Economic evaluation analyses

Multivariable regressions within a generalized linear mixed model (GLMM) framework will be used to generate predicted mean values for each resource/cost category, as well as each effectiveness measure. We will model the person-period over the duration of the intervention and follow-up periods. The final predicted mean values will be estimated via the statistical method of recycled predictions, and standard errors will be derived from non-parametric bootstrapping techniques [61]. QALYs gained will be estimated using the predicted utility values from the PROPr and the area-under-the-curve method, while other effectiveness and cost measures will be summed and tested over the intervention phase, as well as the entire observation period. The predicted mean values for each phase will be used to generate ICERs for each of the 3 effectiveness outcomes and each of the 3 perspectives. Cost-effectiveness acceptability curves will then be created to assess the uncertainty surrounding each ICER, as they illustrate the probability that the intervention is cost-effective across a range of value thresholds that reflect a decision-maker’s willingness-to-pay for a unit of effectiveness. One-way sensitivity analyses will be conducted to assess uncertainties related to assumptions, parameter estimates, and model specifications.

### Oversight and management

#### Composition of the coordinating center and trial steering committee

The trial Clinical Coordinating Center (CCC) and Data and Statistics Center (DSC) will be The Emmes Company. The trial steering committee will include lead investigators, the national project director, the CCTN scientific officer, members of the CCC and DSC, and other members of the data, monitoring, and compliance teams. The steering committee will meet weekly to discuss trial progress, protocol deviations, and other matters

#### Composition of the data monitoring committee, its role and reporting structure

The independent CTN Data and Safety Monitoring Board (DSMB) will regularly review accumulating safety and efficacy data to ensure participant protection while meeting the study’s scientific objectives. The DSMB is responsible for conducting periodic evaluations to determine whether the trial should continue as planned, be modified, or be halted. Decisions may be based on concerns related to participant safety, evidence regarding the efficacy of the intervention, or issues with trial performance, such as inadequate recruitment. Reports summarizing safety and efficacy findings will be prepared for DSMB meetings at a frequency of no less than once per year.

#### Adverse event reporting and harms

This low-risk study will not involve investigational drugs or devices, so no causally related adverse events (AEs) or serious adverse events (SAEs) are expected or will be monitored. Safety reporting will focus only on targeted safety events (TSEs): emergency department visits, hospitalizations, overdoses, suicidal ideation, and deaths. These will be documented on designated forms and entered into the Advantage eClinical system. The Clinical Coordinating Center will report TSEs to the NIDA and the DSMB. All study sites have established procedures for managing medical and psychiatric emergencies, which staff will continue to follow. Site treatment providers will monitor participants for clinical deterioration or other concerns and take appropriate action when necessary.

#### Plans for communicating important protocol amendments to relevant parties

Any amendments to the protocol or consent will be approved by the IRB prior to implementation. Participants will be reconsented if the consent is amended to include new risk information (e.g., changes in the anticipated risks/benefits of participation) or other information that involves significant changes to the procedures of the study. Protocol updates will be posted to clinicaltrials.gov.

#### Data collection, quality, and management

A centralized DSC oversees data management, including developing and validating eCRFs, the study database, and training site staff. Advantage eClinical is used for data entry, and QualtricsXM for SIRI team member assessments. Sites enter accurate, complete data from source documents into eCRFs by authorized staff, following DSC guidelines. The DSC provides data dictionaries, user guides, and instructions, and conducts ongoing validation, discrepancy checks, and audits comparing source data to eCRFs. Queries are issued for missing or inconsistent data, and progress/quality reports posted daily to a secure site. Participant data uses unique study IDs and systems are password-protected. Upon completion, the DSC will clean, lock, and archive datasets, providing both raw and de-identified versions to NIDA. Training covers assessments, eCRF use, and quality standards, with data monitored to meet predefined quality thresholds.

#### Data sharing and dissemination

This study will comply with the NIH Data Sharing Policy and Implementation Guidance. Investigators will register and report results of the trial in ClinicalTrials.gov, consistent with the requirements of the Policy on the Dissemination of NIH-Funded Clinical Trial Information and the Clinical Trials Registration. Primary data for this study will be available to the public in the NIDA data repository, per NIDA CTN policy. The primary outcome publication will be included along with study underlying primary data in the data share repository, and it will also be deposited in PubMed Central, per NIH Policy. The planning, preparation, and submission of publications will follow the policies of the Publications Committee of the CTN.

#### Confidentiality

Participants will provide written informed consent and complete HIPAA Authorization and/or EHR release forms. Only authorized personnel will have access to identifiable data, which is encrypted and stored securely. IRBs, regulatory agencies, and sponsors may inspect records for compliance. Participants will be assigned unique study IDs. Records will be retained for at least 3 years post-study, or longer per IRB/state/federal requirements.

## Discussion

The HI-SIRI study will serve as a major advancement in addressing the complex health needs of PWID suffering from infectious diseases. If the intervention is proven effective in reducing the rate of readmissions and mortality, the HI-SIRI study could transform the treatment of PWID experiencing SIRIs.

The pilot program conducted by the Miami SIRI team demonstrated promising results, with high rates of antibiotic completion and MOUD uptake, reduced patient-directed discharges, and lower readmission rates compared to historical controls. These outcomes highlight the potential efficacy of the integrated care model in managing PWID with SIRIs and addressing the broader syndemic of infectious diseases and SUDs. However, that pilot work was limited by non-randomized evaluation and study at a single hospital site. The multicenter randomized controlled trial design of the HI-SIRI study allows for a robust evaluation of the intervention’s effectiveness across diverse geographic locations and healthcare settings. By including sites with varying levels of access to SUD treatment and differing local health policies, the study aims to maximize external validity and generalizability.

One of the primary strengths of the HI-SIRI study is its focus on patient-centered care and adaptation to the needs of the individual. The intervention team tailors antibiotic treatments and SUD management to the individual needs of each participant, considering their social circumstances and preferences [49]. This approach is crucial for engaging PWID, who often face stigma, discrimination and barriers to accessing healthcare [18, 69–71]. The inclusion of harm reduction principles further supports the goal of reducing preventable morbidity and mortality without requiring abstinence from drug use [51]. In contrast to many SUD and infectious disease clinical trials, HI-SIRI will be testing a model of care, rather than a particular medication or specific behavioral therapy. The study will not directly pay for medical care/medications but rather will work within the existing healthcare structure to fund treatments using existing means. The study’s comprehensive implementation evaluation will provide valuable insights into implementation challenges of the integrated care model and potential implementation strategies for future testing, if the intervention is shown to be effective. Understanding these factors is essential for scaling up the intervention and ensuring its long-term success in various healthcare settings. Additionally, cost effectiveness evaluation of the intervention will help determine how this more intensive—and possibly costly—treatment model measures against potential healthcare cost savings of readmissions.

The SIRI team intervention personnel includes clinicians with dual expertise in infectious disease management as well as addiction medicine [41]. The addition of patient navigators, most of whom have lived experience with SUD, further strengthens the ability of the team to connect with a population that often harbors mistrust of healthcare providers. Team members will meet participants at the bedside and continue to build trust and support after hospital discharge, throughout the 4-month intervention period.

Further strengths include the unique patient population, broad substance use inclusion criteria, and a non-abstinence-based primary outcome. PWID hospitalized with infectious diseases have been underrepresented in broader infectious disease clinical trials. For example, the largest randomized trial in endocarditis included only 5 out of 400 patients with a history of IDU [72]. There is great interest in the ID community in implementing more diverse infection treatments, such as oral antibiotics for invasive infections and long-acting injectable antibiotics, for PWID, yet very little has been done in the way of prospective research to inform these approaches [73]. There is great interest in medical treatment of OUD, for which we have highly effective pharmacotherapy [74], but less data on approaches to management of infectious diseases in the face of stimulant use disorder, despite worse clinical outcomes [75]. Consistent with the fourth wave of the overdose crisis, we expect our cohort will include many with co-use of opioids and stimulants [76]. There will also be persons who only use stimulants, for whom SIRI treatments are understudied. In keeping with a trial rooted in harm reduction, the primary outcome does not rely upon any measures of substance use. The primary goal of the trial is to test whether the compassionate, nonjudgmental, patient-centered approach to SUD and infectious disease care can be successful in keeping people alive (the overarching goal of harm reduction) and out of the hospital during a vulnerable period.

Despite the promising pilot study results, success in the HI-SIRI study faces several challenges and potential limitations. The non-blinded nature of the trial may introduce bias, and the reliance on self-reported data for some outcomes could affect the accuracy of the findings; however, self-reported healthcare utilization will be validated against medical record abstraction. The intervention involves substantial contact with the medical team, which could be costly, especially physician involvement. While we do not expect any cross-over of TAU participants into the intervention arm, the development of local SIRI teams, clinician peer education, and leadership could bleed over into the TAU arm with potential to dilute the effect of the intervention. For example, a SIRI team might create an infectious disease screening order set that could start to be used by physicians caring for TAU participants, thereby improving infection screening in both treatment arms. The impact of having a SIRI team in the hospital will be further characterized in the implementation science component of the trial. Finally, loss to follow up is common in trials involving individuals with SUD and we expect even higher among PWID hospitalized with infections. In order to mitigate this risk, participants will only be enrolled if they provide at least minimum pre-defined locator information and participants with no phones will be provided with study phones. Furthermore, the primary outcome is available independent of whether a participant is lost to follow up.

If successful, the HI-SIRI study has the potential to significantly impact the care of PWID with SIRIs by providing a holistic, patient-centered approach that integrates infectious disease and SUD treatment with harm reduction strategies. The findings from this study will have the potential to transform our approach to care for PWID with infections, advancing health for a community long left behind in healthcare innovations.

